#### Interim analyses {21b}

Interim analyses are possible, according to time points that are not previously defined. If an interim analysis reveals an undue disadvantage of PGx intervention (e.g., increased number of adverse events) compared to the standard care group, the study will be stopped.

#### Methods for additional analyses (e.g., subgroup analyses) {20b}

Currently, there are no subgroups or adjusted analyses planned. However, the stored samples allow the assessment of additional genetic biomarkers, which may be used for further stratification of the patient cohort and therefore subgroup analyses.

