### Trial design {8}

This is an open-label, randomized controlled trial, investigating the effectiveness and tolerability of registered antidepressants in adult inpatients with diagnosed major depressive episode.

To prevent selection bias, eligible patients in need of a new antidepressant pharmacotherapy are randomized at the same ratio into either the control or the intervention arm (parallel study arms).

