**Fig. 1 Fig1:**
[figure not shown]
Study procedures

**Table 1 Tab1:** Schedule of assessments

Day	Pre-study	Run-in phase		Treatment phase					Follow-up	Clinic discharge
	−8	−7	−7–0	0	7	14	21	28	35, 42..	
Informed consent for trial participation	**x**									
Eligibility (pregnancy test, drug screening, inclusion, & exclusion criteria)	**x**									
Buccal swab (Stratipharm®)		**x**								
Medical history (previous antidepressant therapies)			**x**							
Lab values (basic hematology, creatinine (eGFR), ASAT, ALAT, total bilirubin, gamma-GT, CRP, TSH, vit. B12, and vit. D)			**x**							**x**
Concomitant medication documentation			**x**	**x**	**x**	**x**	**x**	**x**	**x**	**x**
RANDOMIZATION (only if new antidepressant indicated)				**x**						
PGx pharmaceutical recommendation (only arm A)				**x**						
Start NEW antidepressant				**x**						
HAM-D17	**x**			**x**^**a**^	**x**^**c**^	**x**	**x**^**c**^	**x**	**x**	**x**
AE assessment (antidepressant therapy only)					**x**^**c**^	**x**	**x**^**c**^	**x**	**x**	**x**
FIBSER patient self-assessment				**x**^**a**^	**x**^**c**^	**x**	**x**^**c**^	**x**	**x**	**x**
BDI-II patient self-assessment				**x**^**a**^		**x**		**x**	**x**^**b**^	**x**
Blood sample collection (EDTA and serum)						**x**		**x**		

^a^Baseline scoring before the first intake of new antidepressant

^b^BDI-II assessed in two weekly intervals

^c^Only for study arms A and B

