### Assignment of interventions: allocation

#### Sequence generation {16a}

Allocation of participants to study arms A or B is based on a computer-generated allocation sequence without any stratifying factors (static unstratified multi-block randomization).

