### Statistical methods

#### Statistical methods for primary and secondary outcomes {20a}

The primary outcome of this study is the response rate at day 28 in study arms A and B. The response is defined as a reduction of the HAM-D17 score of at least 50% compared to baseline at day 0. Additionally, the following secondary outcomes are assessed: time to response, remission rate, overall change in HAM-D17 score, laytime in the clinic, change in BDI-II score, change in FIBSER score, and number of AEs related to antidepressant pharmacotherapy. For statistical analyses, the software packages of “IBM SPSS Statistics” and “GraphPad Software” are used. A descriptive statistics analysis for all variables is performed. Fisher’s exact test or *t* test is used to compare pairwise differences between groups and between baseline and follow-up visits as per data type. To measure the correlation between variables, the Spearman coefficient will be used. Significance level is two-sided, *α* = 0.05. For further statistical analyses, adjustments for confounding factors will be taken into account. Any deviation from the original statistical plan will be described and justified in the final trial report.

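### The secondary change scores are compared by unadjusted t tests although day-0 scores are collected, and {20a} and {20b} do not agree on whether adjusted analyses are planned

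*Protocol article*

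**What the plan says.** In the Protocol article, Statistical methods {20a} lists among the secondary outcomes "overall change in HAM-D17 score, laytime in the clinic, change in BDI-II score, change in FIBSER score". It names two procedures for comparisons, Fisher's exact test or a t test, and says of them that the "test is used to compare pairwise differences between groups and between baseline and follow-up visits as per data type". No model with a baseline covariate appears anywhere in the article.

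Day-0 values exist for all three scores. The schedule of assessments (Table 1, under Participant timeline {13}) marks HAM-D17, FIBSER and BDI-II at day 0, with the footnote "Baseline scoring before the first intake of new antidepressant". The procedures for arms A and B repeat day 0 for each score.

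On adjustment, {20a} says: "For further statistical analyses, adjustments for confounding factors will be taken into account". Section {20b}, which covers additional analyses, says: "Currently, there are no subgroups or adjusted analyses planned". Neither section names a covariate. Sequence generation {16a} describes a "computer-generated allocation sequence without any stratifying factors", so the randomisation does not supply a covariate by default either.

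**The concern.** A change score uses the baseline value only by subtracting it, which fixes the regression slope of the day-28 score on the day-0 score at 1. ANCOVA estimates that slope from the data. Unless the true slope happens to be 1, the change-score comparison has the larger variance. The plan would then give up precision on three secondary endpoints that it could keep with data already in hand.

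The second issue is the wording on adjustment. One section expects adjusted analyses of some kind and the next says that none is planned. While both statements stand, a later report could adjust or not adjust and claim consistency with the protocol in either case.

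A smaller issue is that {20a} puts comparisons between visits on the same footing as comparisons between arms. A change over time within one arm says nothing about the intervention, because the null hypothesis in Objectives {7} is about a difference between arms.

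**Working it through.** **The plan's own figure.** Sample size {14} gives 95 per arm for response rates of 0.5 and 0.7, two-sided alpha 0.05 and 80% power. The pooled normal-approximation formula gives

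n = [1.96·√(2·0.6·0.4) + 0.8416·√(0.5·0.5 + 0.7·0.3)]² / 0.2² = (1.358 + 0.571)² / 0.04 ≈ 93 per arm,

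and 80.8% power at 95. The stated figure is close to this. It is used below only as the number per arm.

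**Inputs for the change scores.** The arms are allocated 1:1 (Trial design {8}), with 95 per arm and two-sided alpha 0.05. The documents do not give the baseline SD (s0), the day-28 SD (s1) or their correlation (r), so these are assumed and varied.

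**Formulas**, per patient, large-sample, with the same SDs and slope in both arms:

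- Change score: V_c = s0² + s1² − 2·r·s0·s1
- ANCOVA: V_a = s1²·(1 − r²)
- Difference: V_c − V_a = (s0 − r·s1)², which is never negative and is zero only when s0 = r·s1
- With s0 = s1, V_a / V_c = (1 − r²) / [2(1 − r)] = (1 + r)/2
- Power of the change-score t test at the effect for which ANCOVA has 80% power with 95 per arm: Φ(2.80·√(V_a/V_c) − 1.96)
- Number per arm with which ANCOVA matches the t test at 95: 95·V_a/V_c

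**Results**, with s1 = 1:

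| s0/s1 | r | V_c | V_a | V_a/V_c | t-test power when ANCOVA has 80% | ANCOVA n per arm matching 95 |
|---|---|---|---|---|---|---|
| 1.00 | 0.3 | 1.400 | 0.91 | 0.65 | 62% | 62 |
| 1.00 | 0.5 | 1.000 | 0.75 | 0.75 | 68% | 71 |
| 1.00 | 0.7 | 0.600 | 0.51 | 0.85 | 73% | 81 |
| 0.75 | 0.3 | 1.1125 | 0.91 | 0.82 | 72% | 78 |
| 0.75 | 0.5 | 0.8125 | 0.75 | 0.92 | 77% | 88 |
| 0.75 | 0.7 | 0.5125 | 0.51 | 0.995 | 80% | 94.5 |
| 0.50 | 0.3 | 0.950 | 0.91 | 0.96 | 78% | 91 |
| 0.50 | 0.5 | 0.750 | 0.75 | 1.00 | 80% | 95 |
| 0.50 | 0.7 | 0.550 | 0.51 | 0.93 | 77% | 88 |

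**Why the SD ratio matters here.** Eligibility {10} requires a HAM-D17 of at least 17, which may narrow the baseline spread of that score and move it towards the lower rows. Two things limit this. Table 1 scores eligibility at day −8 and baseline at day 0, and BDI-II and FIBSER have no entry cut-off of their own.

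**The two statements on adjustment.** Section {20a} refers to further analyses, and {20b} is the section on additional analyses, so both address the same set. One foresees adjustment and the other says that none is planned at present.

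**The case against.** The strongest reply is that nothing named in {20a} is invalid. Under 1:1 randomisation an unadjusted comparison of changes is unbiased and keeps its type I error, and only secondary endpoints are involved. That stands in full.

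The gain may also be small. A reader might take the equal-SD ratios as equivalent to 33% to 54% more patients (1/0.75 = 1.33, 1/0.65 = 1.54). That holds only if the SDs are equal. With a baseline SD of 0.5 to 0.75 of the day-28 SD and the same correlations, the gain is 0% to 22% (1/1.00 to 1/0.82). The documents do not say which case applies.

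A reader might infer that covariates will be picked once the data are known. The documents do not show this. The two statements are softened, one by speaking of further analyses and the other by speaking of the present. They can be read as unadjusted main comparisons, with nothing else planned yet. Covariates are commonly named in the analysis plan, which is not shown, and {20a} undertakes to justify deviations from it. What remains is loose wording that should be reconciled.

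Three further readings do not hold:

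- Unstratified randomisation over two clinics is not a fault in itself. The test's error rate already allows for chance imbalance, and nothing in the article indicates that response differs between clinics.
- Section {20a} need not mean Fisher's exact test on paired data. It assigns tests by data type, and the listed binary outcomes, response and remission, are each defined at week 4 (Outcomes {12}). No endpoint is specified as a paired binary comparison.
- No case is made here for an adjusted model of the primary endpoint.

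**Conclusion.** The point holds as a matter of efficiency and wording. For the changes in HAM-D17, BDI-II and FIBSER, the named t test is valid but never more precise, in large samples, than ANCOVA on the day-0 score. For assumed correlations of 0.3 to 0.5 the variance ratio is 0.65 to 0.75 with equal SDs, and about 0.82 to 1.00 if the baseline SD is 0.5 to 0.75 of the day-28 SD. The loss therefore runs from none to about a third of the variance, and for HAM-D17 it may be close to none because of the entry cut-off. These figures rest on assumed correlations and SDs, and on a common slope in both arms.

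Sections {20a} and {20b} are in mild conflict on adjusted analyses. The Fisher comparison of day-28 response rates, and the conclusion drawn from it, are not affected.

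**What to change.** 1. In {20a}, replace the t test for the between-arm comparison of changes in HAM-D17, BDI-II and FIBSER by ANCOVA with the day-0 value of the same score as covariate. A mixed model over the scheduled visits with that covariate would also serve, but it would have to be squared with the last-value rule for missing data in {20c}.
2. State that conclusions rest on the between-arm comparison and that changes from baseline within an arm are descriptive.
3. Make {20a} and {20b} say the same thing. If any other adjusted analysis is intended, name its covariates. If none is, remove the sentence in {20a}.
4. Date the change before anyone sees outcome data by arm, including at any interim look under {21b}.

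The cost is analysis wording only, since the day-0 scores are already collected and no visit or patient is added. Recruitment began in September 2020, so this is an amendment to a running open-label trial and should be recorded as one.

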#### Methods in analysis to handle protocol non-adherence and any statistical methods to handle missing data {20c}

Missing data will be retrospectively retrieved from medical records if possible. If the missing data cannot be retrieved, the last observed value will be used for analysis. Study drop-outs are replaced to achieve the final calculated study size of 95 patients per study arms A and B.

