#### Sample size {14}

The sample size was calculated to be 95 patients per study arms A and B. This was done taking into account the following criteria: power = 80%, *α* = 5%, response rate standard care = 0.5 [1, 2] and response rate PGx guided = 0.7 [16]. For the observational study arm, there is no sample size calculation needed, since this arm does not contribute to the primary endpoint.

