#### Plans to promote participant retention and complete follow-up {18b}

Assessments and follow-ups are only conducted during the participants’ inpatient stay at the psychiatric clinic. Therefore, the risk of loss to follow-up and deviation to the protocol due to failure to comply with the study visits are considered negligible. However, patients who withdraw their consent (e.g., refuse further data collection) will be informed that all data collected until the time point of their withdrawal will be kept coded and used for analysis.

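### Read literally, replacing drop-outs up to a final 95 per arm leaves them out of the analysed 95, which conflicts with the rule that withdrawn patients' data are analysed

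*Protocol article*

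**What the plan says.** Three rules in the protocol article bear on who is analysed.

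- Replacement, section {20c}: "Study drop-outs are replaced to achieve the final calculated study size of 95 patients per study arms A and B".
- Missing values, the sentence just before it in {20c}: "If the missing data cannot be retrieved, the last observed value will be used for analysis".
- Withdrawal of consent, section {18b}: these patients are told that "all data collected until the time point of their withdrawal will be kept coded and used for analysis".

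The target comes from section {14}: "The sample size was calculated to be 95 patients per study arms A and B". The article does not define a drop-out, name the set of patients in the primary analysis, or say how a replacement enters the allocation sequence. Section {18b} gives no drop-out rate and describes the risk of loss as negligible, because assessments take place during the inpatient stay.

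**The concern.** If drop-outs must be replaced before a final 95 is reached, they are not among the 95. If their data are analysed, as {18b} says for patients who withdraw consent, they are already among those analysed, and replacement is not needed to reach that number. The rules do not define the same group of patients.

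This affects the primary endpoint. Physicians, patients and HAM-D17 raters all know the allocation (sections {17a}, {18a} and the Discussion), so leaving the study can depend on the arm and on how the patient is doing. Scores are collected only in the clinic, so a discharge before day 28 also removes the day-28 score, and that may happen more often in patients who do well. Replacement restores the number of patients. It does not restore the comparability that randomisation gave to those first allocated. An analyst could also choose between the readings after seeing open-label data.

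**Working it through.** **1. Does the 95 contain a drop-out allowance?** Inputs from sections {14}, {20a} and {8}: "response rate standard care = 0.5", "response rate PGx guided = 0.7", 80% power, α = 0.05 ("Significance level is two-sided"), equal allocation. The usual two-proportion formula, without continuity correction and with mean rate 0.6, is

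n = [1.960·√(2·0.6·0.4) + 0.842·√(0.5·0.5 + 0.7·0.3)]² / 0.2² = 93 per arm.

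At 95 per arm the same approximation gives 80.8% power. The stated figure is reproduced as an uninflated number, so the final size in {20c} is the number needed for analysis.

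**2. The rules side by side.**

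| Rule | Drop-outs in the analysis? | Analysed number |
|---|---|---|
| {20c} replacement, read literally | No | 95 per arm |
| {18b} data up to withdrawal used | Yes, for those who withdraw consent | Above 95 if others are also added |
| {20c} carry-forward | Yes, if it covers drop-outs; it does not say so | As above |

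The first two rows conflict on the text. The third conflicts with the first only if carry-forward is meant for drop-outs and not just for missed visits of patients who stay.

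**3. What exclusion could do.** The documents give no drop-out rate, so the rates here are assumptions. Let p be true response, m the drop-out proportion and r the proportion of drop-outs who would have responded. The rate among those who stay is (p − m·r)/(1 − m). Take p = 0.5 in both arms and r = 0.1:

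- m = 0.05: (0.5 − 0.005)/0.95 = 52.1%
- m = 0.10: (0.5 − 0.01)/0.90 = 54.4%
- m = 0.15: (0.5 − 0.015)/0.85 = 57.1%
- m = 0.20: (0.5 − 0.02)/0.80 = 60.0%

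The two-sided rejection rate of Fisher's exact test, which {20a} lists and which suits a binary endpoint, was found by exact enumeration with 95 analysed per arm:

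| Drop-out in the two arms | Rates among stayers | Spurious difference | Rejection |
|---|---|---|---|
| None | 50.0% vs 50.0% | 0 | 3.5% |
| 5% vs 10% | 52.1% vs 54.4% | 2.3 points | 4.4% |
| 5% vs 15% | 52.1% vs 57.1% | 5.0 points | 7.9% |
| 10% vs 20% | 54.4% vs 60.0% | 5.6 points | 9.0% |

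The arm that loses more patients looks better here because most drop-outs were assumed to be non-responders. If responders left early, the sign would reverse. With equal m and equal r in both arms, the rates among stayers are equal and there is no bias.

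**4. Cost of stopping at 190 randomised with no replacement.** If drop-outs are scored as non-responders, the design rates become 0.5(1 − d) and 0.7(1 − d), where d is the drop-out proportion in each arm. Exact Fisher power at 95 per arm is 76.0% with d = 0, 70.5% with d = 5% (0.475 vs 0.665) and 65.1% with d = 10% (0.45 vs 0.63).

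**The case against.** The strongest reply is that nothing in the article limits the primary analysis to completers or removes a replaced patient. A coherent reading exists: continue the randomisation until 95 per arm have completed, then analyse everyone randomised, carrying the last value forward. Section {18b} supports this, and on that reading the randomised comparison is intact. This stands. A reader might infer from {20c} that the primary analysis is a completers' comparison and that randomisation is broken. The documents do not establish that; it follows only if drop-outs are in fact left out. The benign reading is not stated either, and under it the final 95 would not be the number analysed.

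A reader might also infer that a replacement must be steered into the arm that lost a patient, which a block sequence could not do without breaking concealment. Section {20c} does not say this. The sequence in {16a} can simply continue into both arms.

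Some drop-outs may leave in the run-in, between day −7 and randomisation at day 0. Replacing those does no harm. The wording about arms A and B makes this the less natural reading.

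Finally, the size of the bias rests on assumed rates, while {18b} expects negligible loss. That is fair: 5% versus 10% drop-out leaves rejection below the nominal 5%. But if loss were truly negligible, the replacement rule would have no purpose.

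**Conclusion.** The concern holds as a conflict in the text with conditional consequences. Read literally, the replacement rule puts drop-outs outside the analysed 95. This contradicts {18b} and, if carry-forward is meant to cover drop-outs, the preceding sentence of {20c}.

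Bias arises only if drop-outs are actually excluded and drop-out is both outcome-related and different between arms. Under the assumptions shown, a gap of 10 percentage points in drop-out gives a spurious difference of 5.0 to 5.6 points, and Fisher rejection under the null rises from 3.5% to between 7.9% and 9.0%. Smaller gaps do little. The direction cannot be stated in advance. The point is worth correcting before analysis because it decides who enters the primary comparison, and the correction is cheap.

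**What to change.** In {20c}, replace the sentence on replacement with statements that:

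1. the primary analysis includes every randomised patient in the allocated arm;
2. a drop-out after randomisation remains in the analysis and is never substituted by a later patient;
3. a drop-out's day-28 response is scored by one named rule, for example the stated carry-forward rule or non-response;
4. any further recruitment to offset drop-out continues the same sequence into both arms and adds to those already randomised;
5. a completers' analysis is a sensitivity analysis only.

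The cost is a few sentences, and the number analysed may differ from 95 per arm. As a guide to numbers, 95/(1 − d) gives 100 per arm at an assumed 5% drop-out and 106 at 10%. This keeps about 95 observed day-28 scores per arm but does not recover the power lost if drop-outs are scored as non-responders. If recruitment instead stops at 190, the power in {14} should be restated for the expected drop-out and the chosen scoring rule, because the loss shown in step 4 of the working is not trivial.

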#### Plans to give access to the full protocol, participant level-data, and statistical code {31c}

To grant public access to the study procedure and status, it is registered and updated whenever necessary in the Swiss National Clinical trial Portal (SNCTP000004015) and the ClinicalTrials.gov register (NCT04507555), of which the latter is listed in the WHO International Clinical Trials Registry Platform (ICTRP; http://www.who.int/ictrp/en/).

### Oversight and monitoring

#### Composition of the coordinating center and trial steering committee {5d}

This trial is an investigator-initiated multicenter clinical study. There is no external coordinating center or trial steering committee involved.

#### Composition of the data monitoring committee, its role, and reporting structure {21a}

The local ethics committee classified this trial as low risk. Therefore, internal monitoring by designated personnel is applicable. Internal monitoring is performed after the inclusion of the first participant and after study termination. In between internal monitoring will be applied as needed. The accuracy and completeness of the transfer of data from the original source to the CRF as well as completeness and storage of blood samples are checked. Study relevant source data and documents are accessible to internal monitors and in any case to external auditing. Questions are answered during monitoring and auditing. An internal data monitoring plan has been approved by the local ethics committee prior to study initiation.

#### Adverse event reporting and harms {22}

The intervention under investigation consists of a clinical pharmacist’s service resulting in a recommendation of an antidepressant drug approved in Switzerland. Study procedures include taking a swab of the oral mucosa and drawing blood samples for further analysis. These procedures are considered low-risk and routine clinical practice. Only AEs related to the antidepressant pharmacotherapy are reported, since this is a secondary outcome of the study.

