#### Outcomes {12}

The primary endpoint is defined as the rate of response to the antidepressant therapy at the end of week 4 of the treatment phase. This time point was chosen based on the recommendations of the SGAD, which advise to assess clinical effectiveness after four weeks of antidepressant pharmacotherapy [3]. Moreover, the response is determined as a reduction in the Hamilton Depression (HAM-D) Scale score of at least 50% from the baseline score [18]. In this study, the 17-item HAM-D questionnaire (HAM-D17) is used.

Secondary endpoints will be assessed to further evaluate the clinical effectiveness of pharmacist-guided PGx testing as an intervention in antidepressant pharmacotherapy. Included are the following endpoints: (1) time to response—time span from the start of antidepressant pharmacotherapy until first assessed response (= HAM-D17 reduction of at least 50% compared to baseline), until end of week 4; (2) remission rate—HAM-D17 score ≤ 8, at week 4; (3) overall change in HAM-D17 score from baseline to end of week 4; (4) time till discharge—time span from admission to discharge from inpatient treatment, assessed up to 3 months; (5) patient depression self-rating—two weekly assessment with Beck-Depression-Inventory (BDI-II) questionnaire [19], until end of week 4; (6) side effect measure—weekly assessment of self-rated frequency, intensity, and burden of side effects (FIBSER score) [20], until end of week 4; and (7) Number of AEs related to antidepressant pharmacotherapy—severity grading ≥ 2 (using CTCAE version 5.0) [21] and causality to antidepressant pharmacotherapy assessed as possible, probable, or definite, until end of week 4.

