### Data collection and management

#### Plans for assessment and collection of outcomes {18a}

Outcomes described in section {12} are assessed and collected using validated questionnaires and scoring tools (HAM-D17, FIBSER, BDI-II). FIBSER and BDI-II are patient-self-rated scores where the patients fill the according questionnaires independently [19, 20]. The HAM-D17 score is assessed by a trained rater (e.g., treating physician or specifically designated personnel) [18] who is however, not blinded to the patient allocation. The treating physician does the antidepressant adverse event assessment and grading according to the CTCAE version 5.0 [21]. The described data is collected on paper forms approved by the local ethics committee or directly entered into the patient electronic medical record when appropriate.

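### The adverse-event endpoint counts only events that the unblinded treating physician attributes to the antidepressant, with no day-0 check, so arm-dependent attribution could create or hide a difference in that count

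*Protocol article*

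**What the plan says.** All references are to the protocol article.

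- **Outcomes {12}**, secondary endpoint 7: the number of adverse events (AEs) of CTCAE grade 2 or higher with "causality to antidepressant pharmacotherapy assessed as possible, probable, or definite, until end of week 4". Endpoint 6 in the same list is the weekly self-rated FIBSER side-effect score.
- **Plans for assessment and collection of outcomes {18a}**: "The treating physician does the antidepressant adverse event assessment and grading". No other person is named for the causality judgement.
- **Discussion** and **Who will be blinded {17a}**: the treating physician and the patient know the allocation.
- **Adverse event reporting and harms {22}**: "Only AEs related to the antidepressant pharmacotherapy are reported"; the reason given is that this is a secondary outcome.
- **Table 1**: the AE row is restricted to antidepressant therapy and has entries at days 7, 14, 21 and 28, at follow-up and at discharge. Its day-0 cell is empty. HAM-D17, FIBSER and BDI-II each have a day-0 score before the new drug is first taken.
- **Relevant concomitant care {11d}**: an antidepressant taken before admission may continue during the run-in.
- **Objectives {7}**: tolerability is a secondary objective.
- **Interim analyses {21b}**: the study stops if an interim look shows an undue disadvantage of the intervention, with more adverse events as the example.

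**The concern.** For endpoint 7 the causality judgement acts as a gate: an event counts only if it passes. The gate operates after randomisation, and the person operating it knows the arm. In arm A that person has also received an individualised, genotype-based drug recommendation at day 0, which may make a link to the drug seem less likely, or may make the physician look harder for one. Randomisation balances the true events. It does not balance the judgement.

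The empty day-0 cell widens the room for judgement. A complaint noted at day 7 may come from an earlier antidepressant that was still being taken at day 0. Without an AE list at day 0, the physician must sort old from new by opinion.

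At stake is one of the two tolerability comparisons, and any interim safety look that relies on the same count. The primary endpoint is not affected.

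**Working it through.** **The plan's own figure.** The article gives no AE rate and no calculation for endpoint 7. Its only sample-size figure is 95 per arm for response rates of 0.5 and 0.7, with 80% power and two-sided 5%:

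n = [1.960 × √(2 × 0.6 × 0.4) + 0.842 × √(0.5 × 0.5 + 0.7 × 0.3)]² / 0.2² = (1.358 + 0.571)² / 0.04 ≈ 93.

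Power at 95 per arm is 80.8%. The 95 is not in dispute, and it is the arm size used below.

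**Inputs.** From the documents: 95 per arm, two-sided 5%, and a t test or Fisher's exact test according to data type. Assumed, because the documents give none: the true AE rate, the share of events attributed to the drug in each arm, and the spread of counts (negative binomial, shape 1).

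**1. A difference created by attribution.** The counted mean per patient is the true rate times the attributed share. True rates are equal, so the apparent rate ratio is simply share A / share B. Arm B is held at 60%. False-positive rates of the t test, 20,000 simulated trials per cell:

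| Share in A | Apparent ratio | 0.5 AE per patient | 1 AE | 2 AEs |
|---|---|---|---|---|
| 60% | 1.00 | 5% | 5% | 5% |
| 55% | 0.92 | 6% | 6% | 7% |
| 50% | 0.83 | 9% | 11% | 14% |
| 40% | 0.67 | 23% | 35% | 49% |

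A gap of 5 points does little harm. A gap of 20 points does a lot.

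**2. The same check on patients with at least one event.** Exact enumeration of Fisher's test, true share of patients with an event 50% in both arms, arm B attribution 80%. With 80% in arm A the counted shares are 40% and 40%, and the false-positive rate is 3.3%. With 70% they are 35% and 40%, giving 8.2%. With 60% they are 30% and 40%, giving 25.4%. For true shares of 30% and 70%, the last figure becomes 13.5% and 43.2%.

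**3. A difference hidden by attribution.**
- Suppose arm A truly has 1.5 AEs per patient and arm B has 1. With 60% attributed in both arms the counted means are 0.9 and 0.6, and power is 43%. With 40% in A and 60% in B, both are 0.6 (1.5 × 0.4 = 1 × 0.6). The excess vanishes and the rejection rate is 5%.
- In the other direction, suppose true shares of patients with an event are 30% in A and 50% in B. Fisher's power without the filter is 76.0%. Attribution of 90% in A and 60% in B gives counted shares of 27% and 30%, and power of 5.4%.

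**4. What an all-cause count costs.** Take true drug-related rates of 0.4 and 0.6 and add 0.4 unrelated events per patient in each arm. The means become 0.8 and 1.0, and power falls from 35% to 18%. With 0.3 and 0.6 (0.7 and 1.0 after adding), it falls from 73% to 37%. If the unrelated events are Poisson, so that the totals are less dispersed, the falls are to 24% and 52%.

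**The case against.** Several counter-arguments have force.

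- **FIBSER.** It measures the frequency, intensity and burden of side effects every week, has a day-0 score, and passes through no physician's causality judgement. A reader might infer that the whole tolerability objective rests on the filtered count. The document does not support that. FIBSER does not repair endpoint 7, however: patients also know their arm, and a burden score is not an event count.
- **The stopping rule.** A reader might infer that endpoint 7 drives the stopping rule, or that AEs are its only trigger. The interim section gives more AEs only as an example and does not say which count is used. What stands is that an interim look relying on this count would inherit its weakness.
- **The size of the bias.** No attribution rate is given. The threshold includes a merely possible link, so excluding an event means rejecting even that. In arm A the physician receives a recommendation and remains free to choose otherwise. A claim that arm A is favoured, or favoured by a stated amount, has no support.
- **Later checking.** It would go too far to say that unrelated events are lost for good. The article limits what is assessed and reported, and the medical records may still hold them.
- **Day 0.** The new drug cannot have caused anything before it starts, and concomitant medication and past antidepressants are documented. This narrows the problem, but none of it lists the complaints present at day 0.
- **Replacing the count.** The objective is tolerability of the antidepressant treatment. An all-cause count answers a broader question and has clearly lower power for drug-related differences, so the case for replacing endpoint 7 fails.

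The Discussion admits the lack of blinding in general, but not its effect on which events are counted.

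**Conclusion.** The point holds for endpoint 7. Its written definition makes counting depend on causality judged by an unblinded physician, the AE assessment covers antidepressant-related events only, and there is no AE assessment at day 0. Attribution that differs by arm could therefore create or hide a difference in this count.

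Neither direction nor size can be read from the document. Under the assumptions above (equal true rates of 1 AE per patient, 60% attributed in arm B, negative binomial counts), the false-positive rate runs from about 6% through 11% to 35% as arm A attribution falls from 55% through 50% to 40%. If attribution is the same in both arms, the filter does not create a false difference.

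This is a cheap improvement to a secondary endpoint. It does not show that the tolerability objective or the stopping rule is invalid.

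**What to change.** 1. At the AE visits already in Table 1, record every CTCAE grade 2 or higher event in arms A and B that is new or worse since day 0, whatever its causality, with the causality judgement as a separate field.
2. Add the AE question to the existing day-0 visit, before the new drug is first taken.
3. Keep the related-event count as endpoint 7.
4. Report the all-cause comparison between arms beside it as a prespecified sensitivity analysis, and show both counts in any interim safety look.

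The cost is an amendment to the protocol and case report form and some extra data entry, with no new visit. The all-cause count is noisier, so it complements endpoint 7 and does not replace it. Elicitation and grading remain unblinded, so bias at the grade 2 threshold is not removed.
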